### Eligibility criteria

#### Inclusion criteria

Inclusion criteria for the children are the following:
Children between 3-7 years old by the start of the assessmentHaving a score equal to or higher than the borderline cutoff of the Swanson, Nolan, and Pelham Parent Rating Scale (SNAP) [38], indicating the children had moderate ADHD symptoms

Children with ADHD symptoms of hyperactivity, anxiety, or sleep disturbance will be recruited in this study. We will not restrict the children to have a formal medical certificate since children are usually assessed and diagnosed by professionals after 7 years old; hence, their hyperactivity, anxiety, and sleep disturbance symptoms have not yet received a diagnosis. We will consider these children according to the inclusion criteria.

Inclusion criteria for parents are the following:
Able to communicate using MandarinWilling to learn the knowledge and manipulations of pediatric *tuina* for ADHD symptomsAvailable to take their children to the designated hospital for pattern identification and conduct manipulations at home according to the study processAgree to give informed consent

#### Exclusion criteria

Exclusion criteria for children are the following:
Currently receiving other massage therapiesHaving other developmental disability (e.g., autism spectrum disorders, intellectual disability)Having acute infection diseases (e.g., scarlet fever, chickenpox), hemorrhagic diseases (e.g., bleeding, local places of various kinds of malignant tumor), or dermatological problems (e.g., scald, severe skin lesion, skin infections)Having any severe illness or medical condition that the investigator deems not appropriate to receive pediatric *tuina* (e.g., bone fractures, paraplegia)

Exclusion criteria for parents are the following:
Having any severe psychiatric disorder (e.g., major depressive disorder)Having difficulties to conduct massage therapy due to physical problemsUnable to imitate the manipulations in the videos provided to test the cognitive and learning abilities

#### Withdrawal criteria

Withdrawal criteria for children are the following:
Occurring of severe adverse eventsCommencement of other pharmacological or psychological therapies for ADHD symptoms during the treatment periodReceiving a major surgical intervention that leads to unsuitability for receiving pediatric *tuina*

Withdrawal criterion for parents is the following:
Withdrawal of consent

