### Trial design

This study is a single-center, two-arm, parallel, open-label, pilot randomized controlled trial. Participants (parent-child pairs) will be distributed into the intervention group and the control group at a 1:1 ratio. Parents in the intervention group (*n* = 30) will receive a training of parent-administered pediatric *tuina* and perform manipulations on their child. Parents in the active control group (*n* = 30) will be given an online training session about the skills of interacting with their children and a progressive muscle relaxation exercise. Treatments as usual (TAU) of the preschoolers in both groups will not be intervened during the treatment period.

This study includes a feasibility phase, which is expected to be the first 2 months of data collection treatment period with around eight parent-child pairs. The feasibility stage is designed to preliminary test the logistics of the intervention delivery, and to undertake an early evaluation of the study design of the whole pilot trial.

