#### Active control group: parent-child interaction training

Parents in this group will receive a parent-child interaction training program which includes progressive muscle relaxation exercise training for children and a health education booklet of ADHD and coping skills. The parents in this group will have to complete an online training session of progressive muscle relaxation exercise [39], which aims to help children reach a relaxation state by relaxing their muscles when facing stresses. The health education booklet covers the background knowledge of ADHD, suggestions, and examples of coping skills (e.g., coping skills for reaction to stress and conflict with children) and interaction skill training for parents (e.g., behavior management, self-regulation, improving organization, improving relationship, and use of encouragement) [40]. All the training contents are recommended by the Department of Health, the government of the Hong Kong Special Administrative Region. The training serves as an early intervention, with the emphasis on modifying the improper parenting methods and enhancing the positive parent-child interaction when the children are still at their preschool stage. Parents will be asked to complete an online written test after they have viewed the online training and teaching materials. They will be asked to spend at least 20 min every other day during the treatment period on doing progressive muscle relaxation exercises with their child and record their practice on a logbook (see Additional file 5).

During the study period, the children’s ongoing treatment, such as medications, behavioral therapies, and other services such as mental health service and parents-supporting activities will not be intervened in both groups. Information on their TAU will be recorded, and they will be asked not to start new treatment targeting ADHD symptoms during the study period. For subjects in both groups, they will be considered to have completed the program (completers) if they have attended the training lessons and performed the treatment at home for at least 3 days per week during the 8-week intervention period.

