#### Intervention modifications

The manipulations selected are gentle and safe for preschoolers. It is unlikely that pediatric *tuina* leads to severe adverse events. Any pain or discomfort, if any, during the intervention, are transient and will not bring to serious sequela. If participants withdraw during the treatment period, their reasons of withdrawal and adverse events will be recorded. They will be followed-up until the adverse events resolved.

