## Data analysis and management

### Statistical analysis

Descriptive statistics for sociodemographic variables and clinical variables will be presented. Data will be presented as mean and standard deviation. The feasibility outcomes will be presented as percentage. The SNAP scores between the intervention group and the active control group in week 4 and week 8 will be compared using a linear mixed-effects model. Other analyses include using a linear mixed-effects model to compare the SNAP (for measuring ADHD symptoms), PAS (for measuring anxiety), CSHQ (for measuring sleep disturbance), and PSS (for measuring parental stress) in the intervention group with the control group at all assessment time points. To estimate the changes with time in each group, the repeated measures ANOVA will be used. The effect sizes will be estimated using between-group mean difference divided by a pooled standard deviation.

The analyses will be based on the intention-to-treat approach. Completer analysis will be a secondary analysis. Completer is defined as those who have attended all lessons, practiced the pediatric *tuina* or parent-child interaction training at least 3 times per week during the treatment period, and completed assessment time point. As the sample size is underpowered, all analysis will be presented with 95% confidence intervals to inform the precision of the results. Since data at the pilot stage is preliminary, it should be treated with caution.

All qualitative data, including interview transcriptions, text from self-report questionnaires, and content of parent logbooks, will be analyzed using thematic content analysis, facilitated by NVivo (QSR, Melbourne, VIC). Adaptations and rationale behind all reported changes to the intervention will also be listed, analyzed, and summarized. All interviews will be audio-recorded and transcribed verbatim. The transcripts will be verified for accuracy against the sound files and revisions will be made as appropriate. Any identifiable remarks will be anonymized before transcripts being imported into NVivo.

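### Children who start another ADHD therapy are withdrawn and no week-4 or week-8 scales are provided for afterwards, which fits poorly with the intention-to-treat analysis

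*Protocol article*

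**What the plan says.** All references are to the protocol article.

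- **Withdrawal criteria.** A child is withdrawn on a severe adverse event, on unsuitability after major surgery, or on commencement "of other pharmacological or psychological therapies for ADHD symptoms during the" treatment period. The same section gives withdrawal of consent as the parents' criterion. It does not distinguish stopping the allocated intervention from leaving the study.
- **Intervention modifications.** "If participants withdraw during the treatment period, their reasons of withdrawal and adverse events will be recorded". The next sentence reads: "They will be followed-up until the adverse events resolved". No outcome scale is named.
- **Active control group section, paragraph on both arms.** Existing care continues and is recorded, and families are told that "they will be asked not to start new treatment targeting ADHD symptoms during the study period".
- **Statistical analysis.** "The analyses will be based on the intention-to-treat approach", and "Completer analysis will be a secondary analysis". The SNAP scores of the two groups "in week 4 and week 8 will be compared using a linear mixed-effects model".
- **Feasibility outcomes.** Completion of the study assessments is one of five named feasibility outcomes.
- **Blinding and data management.** Parents, who rate the children, know their arm. Data are collected by e-questionnaire.

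**The concern.** Intention-to-treat calls for outcomes from every randomised pair, whatever treatment follows. Here a treatment decision made after randomisation triggers withdrawal, and the only follow-up described after that runs to the end of any adverse event, not to the week-4 and week-8 assessments. If sites follow the text, the later scales are not collected.

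The loss is unlikely to be random. Families are asked not to start new ADHD treatment, so those who do so anyway plausibly see persistent or worsening symptoms. Parents know their arm, so uptake could differ between arms.

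Two things are at stake. One is the between-group estimate carried forward from the pilot. The other, more directly tied to the pilot's purpose, is the completion figure. A pair withdrawn by rule counts as incomplete although the parent may have been willing to fill in an online form. The main trial would inherit a retention figure that mixes refusal with a protocol rule.

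**Working it through.** **The plan's own figure.** The Sample size section gives 60 in total with 25% dropout. The number before inflation is not stated, but 45 / (1 − 0.25) = 60, so the plan is consistent with 45 evaluable children, or 22.5 per arm. No rate of starting new therapy is given, so every rate below is an assumption.

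**Effect on completion.** Each rule-imposed withdrawal lowers measured completion at a later assessment by 1/60 = 1.7 percentage points. With an assumed 5% in the tuina arm and 15% in control, that is 30 × 0.05 + 30 × 0.15 = 1.5 + 4.5 = 6 pairs, and 6/60 = 10 percentage points.

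**Effect on the estimate, simple approximation.** If only observed week-8 scores are used, bias ≈ (share leaving control − share leaving tuina) × (how much worse leavers score than stayers, in SD). Assumed shares are 10–20% in control and 5–10% in tuina, with a gap of 0.5–1.0 SD:

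- (0.10 − 0.05) × 0.5 = 0.025 SD
- (0.20 − 0.10) × 1.0 = 0.10 SD
- extremes over all combinations: (0.10 − 0.10) × 1.0 = 0 and (0.20 − 0.05) × 1.0 = 0.15 SD

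This ignores the week-4 scores, which the planned mixed model can use.

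**Effect on the estimate, simulation.** Assumptions: standardised scores with higher meaning worse, week-4 to week-8 correlation 0.6, no true difference, 400,000 children per arm, and the worst-scoring share of each arm leaving after week 4. The likelihood-based model is approximated within each arm by regressing week 8 on week 4 among stayers and predicting for all. Entries are tuina minus control in SD, so a positive value counts against tuina.

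| Leaving, tuina / control | Leaving depends on | Observed week 8 only | Model using week 4 |
|---|---|---|---|
| 10% / 10% | week 4 or week 8 | about 0 | about 0 |
| 5% / 15% | week 4 (seen) | 0.10 | 0.00 |
| 5% / 15% | week 8 (unseen) | 0.17 | 0.12 |
| 5% / 25% | week 4 (seen) | 0.18 | 0.00 |
| 5% / 25% | week 8 (unseen) | 0.32 | 0.25 |
| 15% / 5% | week 4 (seen) | −0.10 | 0.00 |
| 15% / 5% | week 8 (unseen) | −0.17 | −0.13 |

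The unseen-score rows are severe, because exactly the worst week-8 scorers leave. On the other hand, the simulation assumes everyone has a week-4 score; a pair withdrawn before week 4 has only baseline to contribute.

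**Comparison with sampling error.** The 95% half-width for a standardised difference is 1.96 × √(2/30) = 0.51 SD at 30 per arm, and 1.96 × √(2/22.5) = 0.58 SD at 22.5 per arm. A bias of 0.12 SD is about a quarter of 0.51.

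**The case against.** The strongest reply is that the loss of outcomes is inferred from silence. The recording sentence sits in a safety paragraph and does not say that nothing else is collected. This is a condensed article, and the flow diagram, assessment schedule and reporting checklist, where follow-up after withdrawal might appear, are not shown. That limits confidence. It does not remove the point, because the article states the withdrawal trigger, the data recorded and the end of follow-up, and these do not fit together with the declared analysis.

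A reader might infer more than the documents support:

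- **That withdrawn pairs leave the analysis set, so intention-to-treat is flatly contradicted.** No text says so. The completer analysis is secondary, and the mixed model can keep baseline and any week-4 scores. What is at risk is later outcomes.
- **That the rule removes the worst responders.** This is plausible but nowhere stated; a family may start another therapy for other reasons.
- **That the bias has a known size and sign.** It does not. Moreover, under an intention-to-treat target the missing values are scores after the added therapy. The Background says that medication acts quickly on core symptoms, so those scores need not be 0.5–1.0 SD worse. The approximation and the simulation do not model this.
- **That the Trial design section conflicts as well.** Its sentence, "Treatments as usual (TAU) of the preschoolers in both groups will not be intervened during the treatment period", concerns ongoing care, which the article distinguishes from newly started treatment.

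It also stands that the request not to start new treatment should keep numbers low, that recorded reasons would allow some separation of withdrawals afterwards, and that the article itself calls the trial underpowered and its data preliminary.

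**Conclusion.** The point holds as a mismatch between three sections, with moderate confidence because parts of the protocol are not visible. Followed as written, the rule gives avoidable and plausibly informative missing outcomes and lowers the assessment-completion figure for a reason unrelated to families' willingness to respond.

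Bias in the SNAP contrast needs two conditions together under the mixed model: unequal withdrawal between arms, and dependence on scores not observed. If either fails, it is about zero. If both hold, it is about 0.1 SD in either direction with 5% against 15% leaving, and more only with a wider imbalance. That is small beside the pilot's own imprecision. The effect on completion is the firmer ground for acting. The point ranks as a recommended improvement, not a must-fix.

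**What to change.** Leave the clinical stopping rules unchanged and reconcile three sections, with about one sentence in each:

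1. **Withdrawal criteria:** separate stopping the allocated intervention from leaving the study.
2. **Intervention modifications:** request the week-4 and week-8 e-questionnaires from every randomised pair that has not withdrawn consent to data collection, and record any new therapy and its start date.
3. **Statistical analysis:** include these pairs in the intention-to-treat mixed model whatever therapy was started, and report rule-imposed withdrawals separately from refusals in the completion and dropout figures.

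The cost is a few more online questionnaires. The trade-off is that the estimates will include the effect of added therapy, which is what an intention-to-treat reading implies and should be stated when results are reported. Since the article describes the trial as open for recruitment, the change is worth making promptly: assessments not requested on time cannot be recovered.

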### Participant recruitment procedure

A total number of 60 children aged 3-7 years will be recruited with one of their parents in this study. Figure 2 shows the recruitment procedure and based on the CONSORT guidelines. A research coordinator will be responsible for obtaining written informed consent and face-to-face screening. Detailed procedures are the following:

#### Recruitment and preliminary screening

The study will be promoted via posters, emails, and phone messages. Contact methods of a research coordinator will be provided. Parents who intend to participate in the study are required to contact the research coordinator via telephone call or WeChat for preliminary screening. Potentially eligible subjects who meet the preliminary criteria will be invited to further procedures.

#### Informed consent and screening

Potentially eligible participants will receive an interview online. A research coordinator will explain the study to the parents and obtain the written informed consent. Further assessments will be conducted based on inclusion eligibility criteria. Parents will be required to imitate two manipulations in a video that is provided by the research coordinator, and they will be excluded if they fail to do imitation. Personal information about participants will be collected. A case report form (CRF) will be performed by the research coordinator.

#### Assigning a study schedule

The research coordinator will assign the baseline assessment, intervention, and follow-up schedule to the eligible participants.

### Sequence generation and allocation

Children with their parents will be randomly divided into the intervention group or the active control group after the completion of baseline assessments. Block randomization will be carried out using MS Excel with a random block size of 4 to 8 at a 1:1 ratio. The allocation code will be enclosed in sequentially numbered opaque envelopes and kept by a coordinator and will dispense a code to each participant upon confirmation of completion of baseline assessment by the research coordinator. The research coordinator will be blind to the study arms, and the PI will not be involved in the post-baseline data collection.

### Blinding

Due to the nature of the intervention (pediatric *tuina*) and the active control intervention (parent-child interaction training), it is impossible to blind the practitioners and the subjects. Therefore, they will not be blinded. However, parents might have questions when filling the rating scales. If they have any problems, they can inquire to the research outcome assessors. For those outcome assessors who are in charge of guiding the parents to fill the questionnaires and collecting data, they will be blinded.

### Interventions

#### Intervention group: parent-administered pediatric tuina

Children in the intervention group will receive parent-administered pediatric tuina during the treatment period. Figure 3 presents the intervention implementation procedure. The parents will attend an online training program (2 training sessions, 5 h in total) to gain the knowledge and basic manipulations of pediatric *tuina* on ADHD symptoms in preschoolers. Contents of the training sessions will cover the manipulations and acupoints that are commonly used in treating ADHD. The instructor will, inspect their practice, and make feedback to them if there is any deviation. At the end of the training sessions, to assess the parents’ mastery of the contents and techniques, the parents will be asked to conduct the manipulations in the prescription (see Additional file 3) in front of the TCM practitioner via online video chat, or take a video of the manipulations in the prescription and submit it to the TCM practitioner for an assessment. Parents who have passed the assessment could the start conducting the intervention at home, while for those who have not passed, they will be asked to receive the training for one more time until they could appropriately conduct the manipulations. Then they will deliver the *tuina* on their child at home in the following 2 months according to the *tuina* prescriptions formulated by the TCM practitioner. The *tuina* prescriptions will comprise the acupoints selected, the corresponding manipulation, conduction frequency, times of each manipulation, and other necessary information. The parents will be told to deliver pediatric *tuina* therapy on their children every other day, with 20-30 min each day. A logbook will be used for recording (see Additional file 4). Videos of the manipulation techniques and relevant teaching materials will be provided to the parents via social media.

**Fig. 3 Fig3:**
[figure not shown]
Illustration of intervention procedure to parents

#### Active control group: parent-child interaction training

Parents in this group will receive a parent-child interaction training program which includes progressive muscle relaxation exercise training for children and a health education booklet of ADHD and coping skills. The parents in this group will have to complete an online training session of progressive muscle relaxation exercise [39], which aims to help children reach a relaxation state by relaxing their muscles when facing stresses. The health education booklet covers the background knowledge of ADHD, suggestions, and examples of coping skills (e.g., coping skills for reaction to stress and conflict with children) and interaction skill training for parents (e.g., behavior management, self-regulation, improving organization, improving relationship, and use of encouragement) [40]. All the training contents are recommended by the Department of Health, the government of the Hong Kong Special Administrative Region. The training serves as an early intervention, with the emphasis on modifying the improper parenting methods and enhancing the positive parent-child interaction when the children are still at their preschool stage. Parents will be asked to complete an online written test after they have viewed the online training and teaching materials. They will be asked to spend at least 20 min every other day during the treatment period on doing progressive muscle relaxation exercises with their child and record their practice on a logbook (see Additional file 5).

During the study period, the children’s ongoing treatment, such as medications, behavioral therapies, and other services such as mental health service and parents-supporting activities will not be intervened in both groups. Information on their TAU will be recorded, and they will be asked not to start new treatment targeting ADHD symptoms during the study period. For subjects in both groups, they will be considered to have completed the program (completers) if they have attended the training lessons and performed the treatment at home for at least 3 days per week during the 8-week intervention period.

